**Innovative Treatments in Pneumonia 2**

## ABBREVIATIONS AND ACRONYMS

AE adverse events

AIDS Acquired Immunodeficiency Syndrome

BDH Bwaila District Hospital

BMGF Bill & Melinda Gates Foundation

CFR Code of Federal Regulations

CI confidence interval

COM College of Medicine

COMREC College of Medicine Research and Ethics Committee

CRF case report form

CRO contract research organization

DSMB Data and Safety Monitoring Board

DT dispersible tablets

GCP Good Clinical Practices

HIV Human Immunodeficiency Virus

ICF informed consent form

ICH International Conference on Harmonisation of Technical Requirements for Registration of Pharmaceuticals for Human Use

ID identification

IEC independent ethics committee

IMCI Integrated Management of Childhood Illness

IRB institutional review board

ITIP Innovative Treatments in Pneumonia

KCH Kamuzu Central Hospital

kg kilogram

mg milligram

LAR legally authorized representative

MOH Ministry of Health

mRDT malaria rapid diagnostic test

OPD outpatient department

OR odds ratio

PI principal investigator

RR risk ratio

SAE serious adverse event

SC Save the Children Federation, Inc.

SAP Statistical Analysis Plan

SOP standard operating procedure(s)

U.S. FDA United States Food and Drug Administration

UNC University of North Carolina

UW University of Washington

WHO World Health Organization

## EXECUTIVE SUMMARY

**Problem to be studied:** Pneumonia is responsible for more than one in five child deaths around the globe. Each year, approximately 1.1 million children die before their fifth birthdays due to pneumonia, more than the number of under-five deaths that result from human immunodeficiency virus (HIV), tuberculosis, and malaria combined. In addition to preventing pneumonia, there is a critical need to provide greater access to appropriate and effective treatment. Studies in Asia have evaluated the effectiveness of 3 days of oral amoxicillin for the treatment of fast-breathing pneumonia; however, further evidence is needed to determine if 3 days of oral amoxicillin is also effective for the treatment of chest-indrawing pneumonia. Finally, given the paucity of data from Africa, African-based research is necessary to establish optimal treatment regimens for childhood pneumonia in the region.

With the expressed support of the Malawi Ministry of Health (MOH) and in collaboration with external experts from the University of Washington (UW), Save the Children Federation, Inc. (SC) will work closely with investigators at the College of Medicine (COM) at the University of Malawi and the University of North Carolina (UNC) Project to build evidence regarding appropriate duration of treatment with amoxicillin dispersible tablets (DT) for chest-indrawing childhood pneumonia in malaria-endemic settings in Africa. An expanded evidence base will contribute to future iterations of integrated community case management guidelines, which in turn will test innovative approaches to childhood pneumonia treatment.

**Type of research:** The proposed approach involves conducting a double-blinded, randomized, non-inferiority trial with the objective to assess the effectiveness of shorter duration amoxicillin DT treatment of chest-indrawing childhood pneumonia in a malaria-endemic region of Malawi.

**Objectives:** The primary objective of this study is to determine whether 3 days of treatment with oral amoxicillin DT in HIV-negative children 2 to 59 months of age with chest-indrawing pneumonia is as effective as 5 days of treatment.

**Methodology:** The study will enroll 2,000 children presenting to Kamuzu Central Hospital or Bwaila District Hospital in Lilongwe, Malawi. Each child will be randomized to either 3 days of amoxicillin DT followed by 2 days of placebo DT or 5 days of amoxicillin DT. Children in the study will be hospitalized for 48 hours after enrollment and will have scheduled study visits at days 2, 4, 6 and 14.

**Expected findings and their dissemination:** We predict that the rates of treatment failure will be similar in both arms and that 3 days of treatment will be non-inferior to 5 days of amoxicillin DT for chest-indrawing pneumonia. Findings from this study will be disseminated through a peer-reviewed journal and shared with the scientific community.

## PROTOCOL OUTLINE

| | **Title:** | **Innovative Treatments in Pneumonia (ITIP) 2**: Double-blind randomized controlled clinical trial of 3 days versus 5 days amoxicillin DT for chest-indrawing childhood pneumonia among children 2-59 months of age presenting to Kamuzu Central Hospital in Lilongwe, Malawi | | --- | --- | | **Sponsor:** | Save the Children Federation, Inc. (SC) | | **Collaborating Organizations:** | Save the Children International – Malawi Country Office  University of Washington (UW)  Malawi Ministry of Health (MOH)  College of Medicine (COM) at the University of Malawi  University of North Carolina (UNC) Project, Lilongwe Medical Relief Fund Trust  Kamuzu Central Hospital (KCH)  Bwaila District Hospital (BDH) | | **Funding Source:**  **Study Products:** | Bill and Melinda Gates Foundation (BMGF)  3 days of 250 mg amoxicillin DT followed by 2 days of placebo DT (intervention) vs 5 days (control) of 250 mg amoxicillin DT in two divided doses based on age bands (500 mg/day for children 2 months up to 12 months, 1000 mg/day for children 12 months up to 3 years, and 1,500 mg/day for children 3 years up to 5 years of age) | | Rationale: | Build evidence regarding appropriate duration of treatment with amoxicillin DT for chest-indrawing childhood pneumonia in a malaria-endemic setting in Africa | | **Population:** | 2,000 HIV-1 seronegative children, ages 2-59 months of age with chest-indrawing pneumonia | | **Schema:** | Eligible volunteers will be randomized in a double-blinded manner in a 1:1 ratio as follows:  ITIP2: chest-indrawing   | Study groups | N | Day 1 | Day 2 | Day 4 | Day 6 | Day 14 | | --- | --- | --- | --- | --- | --- | --- | | 3 days amoxicillin DT  + 2 days placebo DT | 1,000 | X | X | X | X | X | | 5 days amoxicillin DT | 1,000 | X | X | X | X | X | | | **Objectives:** | 1. Primary: treatment effectiveness 2. Secondary: clinical relapse, treatment failure or clinical relapse, adverse events (AEs) and serious adverse events (SAEs); cofactors of malaria, wheeze, oxygen saturation level <93%, moderate malnutrition, very fast-breathing, and age | | **Endpoints:** | 1. Primary:    - Proportion of children failing treatment 2. Secondary:    - Proportion of children with clinical relapse    - Proportion of children with clinical relapse or treatment failure    - Proportion of children with AEs and SAEs    - Proportion of children failing treatment among those testing positive for malaria (overall)    - Proportion of children failing treatment among those with wheeze    - Proportion of children failing treatment among those with oxygen saturation <93%    - Proportion of children failing treatment among those with mid-upper arm circumference (MUAC)-defined moderate malnutrition (11.5-13.5cm)    - Proportion of children failing treatment among those with very fast-breathing for age (>70 breaths per minute for 2–11 months, >60 breaths per minute for 12–59 months)    - Proportion of children failing treatment by age | | **Timeline:** | Projected duration of enrollment is about 30 months.  All children will be followed for 14 days after randomization. | |
| --- | --- | --- | --- | --- | --- | --- | --- | --- | --- | --- | --- | --- | --- | --- | --- | --- | --- | --- | --- | --- | --- | --- | --- | --- | --- | --- | --- | --- | --- | --- | --- | --- | --- | --- | --- | --- | --- | --- | --- | --- | --- |

**Innovative Treatments in Pneumonia 2**

# BACKGROUND AND INTRODUCTION

The burden of childhood pneumonia remains high, and improved access to effective treatment saves lives. Because vaccines cannot prevent all episodes of pneumonia and because pneumonia incidence remains unacceptably high, there is an urgent need to focus on effective and affordable treatment. Treatment of bacterial pneumonia requires an effective antibiotic used in adequate doses for an appropriate duration. The recommended duration of treatment currently ranges between 5 and 14 days. Shorter duration of therapy, if found to be sufficiently effective, could be particularly important in resource-limited settings where there is a high risk of death, poor access to medicines and health care, and limited budgets for medicines. A shorter antibiotic course is much simpler to administer and is more likely to have improved patient adherence compared to a longer course of treatment when delivered in a community setting. Using a study in Zambia of fast-breathing pneumonia as an example of pneumonia treatment in an outpatient setting, researchers identified only 54% adherence to all doses for 5 days of treatment while observing 76% adherence for 3 days of treatment.[1] Improved patient adherence could also prevent the emergence of antibiotic resistance as well as reduce the rates of adverse events associated with antibiotics. Most importantly, it would reduce the burden on the health systems in resource-limited settings by driving down the costs associated with treatment of childhood pneumonia.

Amoxicillin is recommended as the first-line treatment for fast-breathing and chest-indrawing childhood pneumonia.[2][3] For the treatment of chest-indrawing childhood pneumonia, the World Health Organization (WHO) has revised pneumonia case management guidelines, including a new classification of pneumonia severity and a change in first-line antibiotic therapy. Evidence has emerged that has prompted the development of these revised guidelines. In addition to showing that amoxicillin is superior to cotrimoxazole for the treatment of fast-breathing pneumonia, the data show that oral amoxicillin is equivalent to injectable penicillin for the treatment of chest-indrawing pneumonia. A multicenter, randomized, open-label trial conducted by the WHO Acute Paediatric Pneumonia I Study Group at nine tertiary health facilities in eight developing countries compared the efficacy of a 5-day course of oral amoxicillin versus injectable penicillin in 1,702 children aged 3 to 59 months with chest-indrawing pneumonia.[4] The study found treatment failure rates of 19% at 48 hours in each treatment group (n=161 penicillin; n=167 amoxicillin; risk difference -0.4%; 95% CI 4.2–3.3). In England, the PIVOT trial compared a 7-day course of oral amoxicillin versus intravenous benzyl penicillin for the treatment of severe pneumonia and found that among children with radiologically confirmed pneumonia, the two treatments were equivalent, each having a median time of 1.3 days to achieve the primary outcome of temperature below 38°C for 24 continuous hours.[5] In a multicenter, randomized, open-label equivalency trial, the NO-SHOTS study in Pakistan compared high-dose oral amoxicillin (80-90 mg/kg/day) in a twice-daily regimen over 5 days versus 2 days of injectable ampicillin followed by 3 days of high-dose oral amoxicillin in children with chest-indrawing pneumonia; findings showed that amoxicillin given orally twice a day was equivalent.[6] At day 6, there were 87 (8.6%) treatment failures in the hospitalized group and 77 (7.5%) treatment failures in the home-treatment (oral amoxicillin) group (risk difference 1.1%; 95% CI -1.3–3.5).

In two cluster-randomized community-based trials in Pakistan, oral amoxicillin administered in the community was found to be as effective as standard treatment with a first dose of cotrimoxazole and referral to a facility.[7] In these two studies, 7,621 children aged 2 to 59 months with chest-indrawing pneumonia were either given oral amoxicillin (80-90 mg/kg/day in two divided doses) for 5 days (intervention) or the standard treatment of care at the time - a first dose of oral cotrimoxazole followed by referral to the nearest health facility (control). Treatment failure rates by day 6 were significantly reduced in the intervention clusters compared to control clusters (9% versus18%; risk difference 8.9%) in Haripur District.

Based on the evidence above, the WHO found that in a programmatic context, the distinction between previously defined “non-severe pneumonia” and “severe pneumonia” lost its significance. The revised classification now includes only two categories of pneumonia: 1) “pneumonia” with fast-breathing and/or chest-indrawing, which requires home therapy with oral amoxicillin; and 2) “severe pneumonia,” pneumonia with any general danger sign, which requires referral and injectable therapy.[8] This approach is intended to greatly simplify the management of childhood pneumonia, which will result in a substantially lower need for referral and better treatment outcomes. In the new guidelines, one important distinction between the treatment of fast-breathing and chest-indrawing pneumonia is the duration of oral amoxicillin administration: 3 days for fast-breathing pneumonia cases in areas with low HIV prevalence and 5 days for cases of chest-indrawing pneumonia. With the recent release of the revised WHO guidelines, there is a need to see if a 3-day course of amoxicillin given twice a day is as effective as a 5-day course in the treatment of chest-indrawing pneumonia.

# RATIONALE

There is a critical need for African-specific data, as countries in Africa, including Malawi, endeavor to put into place evidence-based policies and treatment guidelines informed by the local context. There is also a need for local studies in malaria-endemic settings in Africa using child-friendly amoxicillin DT, which the WHO has established as the optimal product formulation for first-line treatment of pneumonia in children less than 5 years of age. [18] [19] [20] This innovation in first-line antibiotic treatment—being flexible for dose adjustment while remaining within the effective therapeutic range—represents major life-, resource-, and cost-savings to families, health facilities, communities, and local governments. Oral amoxicillin DT is safe and well tolerated. Common side effects typically include rashes, nausea, vomiting, and diarrhea. Oral amoxicillin DT can be easily administered by caregivers in the home, making treatment simpler. However, many settings have been slow to adopt the WHO recommendations on oral amoxicillin as an at-home treatment for pneumonia. The clinical trial described in this protocol intends to provide evidence that could improve access to care by improving case management of pneumonia at the household level, which will lead to improved drug adherence and significantly reduce childhood pneumonia deaths.

# STUDY HYPOTHESIS, OBJECTIVES AND ENDPOINTS

## Study Hypothesis

3 days is non-inferior to 5 days of amoxicillin DT treatment for chest-indrawing pneumonia.

## Study Objectives

The broad objective of this study is to provide scientific evidence assessing the optimal duration of treatment with amoxicillin DT for chest-indrawing childhood pneumonia in the malaria-endemic setting in Malawi, Africa.

- - Primary Objective
    - To determine whether 3 days of treatment with oral amoxicillin DT in HIV-negative children 2 to 59 months of age with chest-indrawing pneumonia is as effective as 5 days of treatment.
  - Secondary Objectives
    - To determine whether the intervention arm has equivalent rates of treatment relapse as the control arm among those without treatment failure before or on day 6.
    - To determine whether the intervention arm has equivalent rates of combined treatment failure and relapse before or on day 14 as the control arm.
    - To determine whether the intervention arm has equivalent rates of adverse events (AEs) and serious adverse events (SAEs) as the control arm.
    - To investigate whether there may be a differential treatment response in children who test positive for malaria at baseline. This information will be useful to plan further childhood pneumonia and malaria integrated interventions in similar settings.
    - To determine whether there is a differential treatment response in enrolled children with wheeze during screening (identified prior to any bronchodilator administration).
    - To determine whether there is a differential treatment response in enrolled children with an oxygen saturation level <93% by pulse oximetry at baseline.
    - To determine whether there is a differential treatment response in enrolled children with mid-upper arm circumference (MUAC)-defined moderate malnutrition at baseline (11.5-13.5cm).
    - To determine whether there is a differential treatment response in enrolled children with very fast-breathing for age at baseline (>70 breaths per minute for 2–11 months, >60 breaths per minute for 12–59 months).
    - To determine whether there is a differential treatment response by age.

## Study Endpoints

- - Primary Endpoints
    - Proportion of children failing treatment, defined as the development of any of the following criteria during the specified time periods:

Any time before or on day 6:

- - - - WHO Integrated Management of Childhood Illness (IMCI) danger signs
      - Severe respiratory distress (e.g., grunting, nasal flaring, head nodding, or severe chest-indrawing).
      - Oxygen saturation < 90% by pulse oximetry
      - Vomiting within 30 minutes of 3 or more scheduled (i.e., not repeat) dose administrations of study product
      - Change in antibiotics prescribed by a study clinician (e.g., switch to a second-line antibiotic or prescription for onset of a co-infection)
      - Death

At or after initial hospitalization discharge assessment (between 42 and 60 hours post-enrollment):

- - - - Documented axillary temperature > 38 ºC with chest-indrawing

At day 6 outcome assessment:

- - - - Documented axillary temperature > 38 ºC
      - Chest-indrawing
  - Secondary Endpoints
    - Proportion of children with clinical relapse between treatment failure assessment and day 14 follow-up visit among all children without treatment failure before or on day 6.
    - Proportion of children with either treatment failure or clinical relapse before or on day 14 (among all randomized children).
    - Proportion of children with AEs and SAEs.
    - Proportion of children with treatment failure among those testing positive for malaria by rapid diagnostic testing (mRDT) at baseline (overall).
    - Proportion of enrolled children failing treatment among those with wheeze during screening (identified prior to administration of bronchodilators).
    - Proportion of enrolled children failing treatment among those with oxygen saturation <93% by pulse oximetry at baseline.
    - Proportion of children failing treatment among those with MUAC-defined moderate malnutrition (11.5-13.5cm).
    - Proportion of children failing treatment among those with very fast-breathing for age (>70 breaths per minute for 2–11 months, >60 breaths per minute for 12–59 months).
    - Proportion of children failing treatment by age at baseline.

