## Management of Study Participants During Hospitalization

All children enrolled in this chest-indrawing study (ITIP2) will be initially admitted to the hospital for 2 days, to be assessed by study staff for discharge on the morning of Day 3, between 42 and 60 hours after admission. Discharge criteria will be met if none of the criteria for treatment failure are present. Note that due to logistical or social factors (e.g., caregiver not present, lack of transport options at that time of day), some children who meet discharge criteria might not leave the hospital until after the 60 hour window. When confirmed by a study investigator, such children will not qualify as failing treatment, so long as they do not meet any of the other treatment failure criteria.

Children will be primarily managed by study clinicians during any hospitalization, including ward rounds and clinical assessments. Diagnostic tests and medication for intercurrent illnesses will be ordered per ward protocols with results documented in study files. This includes antibiotic treatment regimen changes. To ensure adherence to study protocol, study staff will administer study drugs to participating children during any hospitalization. Study clinicians will be informed by hospital clinicians about the clinical care of children in the study and any clinical decisions made by hospital staff. Study staff will be responsible for orders in the event that study-related laboratory tests and specimen collection are required. In addition to all study staff, all KCH clinicians and nurses will undergo GCP training.

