  - Any time before or on day 6: WHO IMCI danger signs, severe respiratory distress (e.g., grunting, nasal flaring, head nodding, or severe chest-indrawing), oxygen saturation by pulse oximetry < 90%, missing 3 or more doses due to vomiting, change in antibiotics prescribed by a study clinician, or death.
  - At or after initial hospitalization discharge assessment (between 42 and 60 hours post-enrollment): documented axillary temperature > 38 ºC with chest-indrawing.
  - At day 6 outcome assessment: persistence of chest-indrawing, or axillary temperature > 38 ºC.
  - For the purposes of this protocol, children who do not fail on assessment at day 6 will be considered clinically cured. Loss to follow-up or withdrawal from the study at any time after enrollment and before the day 14 follow-up visit will be considered missing outcome data for that respective time point.
- *Clinical relapse* will be defined as recurrence of signs of chest-indrawing pneumonia, severe respiratory distress (e.g., grunting, nasal flaring, head nodding, or severe chest- indrawing) or severe disease after day 6 among those who did not have treatment failure at or by day 6.

Recruitment and follow-up is expected to continue until the maximum sample size is achieved. For the chest-indrawing pneumonia study a total of 2,000 children (1,000 per treatment group) will be enrolled. We are assuming a treatment failure rate of 8% in the 5-day control group and a relative 1.5 non-inferiority margin. Figure 3 shows the maximum true failure rate in the 3-day treatment group in reference to various possible failure rates in the 5-day treatment group and a 1.5 relative non-inferiority margin (50% relative increase in failure rate) that would result in a 95% confidence interval at maximum enrollment which excludes the non-inferiority margin. The figure also indicates the power the study has to show non-inferiority if the failure rates are exactly the same in the two treatment groups for various possible failure rates. Of note, the estimated power is adjusted for a 5% loss to follow-up rate in each of the arms. This is considered conservative with respect to the multiple imputation procedure that will be used to account for missing outcome values.

**Figure 3.** Chest-indrawing pneumonia failure rates

Note:

- Blue, solid circles, blue number below: Potential failure rates for the 5-day treatment group.

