## Protection against Risks

- - Randomization arms

In order to minimize the risk of adverse events, treatment failure, hospitalization, and death, eligibility criteria for this study have been carefully selected and a robust safety monitoring scheme is in place. The children with pneumonia most at risk of treatment failure and/or death will be excluded from this study, including those with WHO IMCI danger signs and HIV infection or exposure. Safety monitoring for this study includes frequent clinical examination at study visits for the first four days, outcome assessment and a clinician on call via an emergency hotline for the first fourteen days, treatment and tracking of all AEs and SAEs, and an external DSMB for regular review of cumulative safety and study conduct data. Refer to Section 4.10 of this protocol for more detail on the study’s Safety Assessments and Reporting procedures.

- - Coercion

In order to minimize the risk of coercion, study staff will not be recruiting participants directly. Instead, OPD clinicians will inform caregivers about the study and refer only those who are interested. During the informed consent process, study staff will emphasize that the child will receive medical care whether enrolled in the study or not.

- - Specimen Collection

In order to minimizing the risks associated with phlebotomy, all study staff who will be collecting specimens from children in the study will be trained in the appropriate procedures and supervised accordingly.

- - Medical Management

In order to minimize the possibility that participation in this trial will interfere with the medical management of children with pneumonia at KCH, study staff will have the primary responsibility for the clinical management of hospitalized children. Hospitalized children (e.g., during the first two days) will be treated and managed by study staff in accordance with standard procedures. Study staff will be informed about any decisions regarding treatment failure and changing antibiotic regimens made by KCH staff. Please refer to Section 4.6 Study Procedures for further description of Management of Study Participants During Hospitalization.

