# Protocol Appendix III: Study requirements and training

Additional study requirements not already described in the protocol are summarized below.

- **Personnel**

The study team on-the-ground will consist of full-time employees in the following capacities:

- - Study coordinator: clinician who will oversee daily study operations and monitor the safety of participants
  - Study medical officers/clinical officers: clinicians whose daily work will involve screening potential study participants, enrolling children into the study, performing clinical assessments during observation periods, clinically managing hospitalized study participants, and conducting the safety monitoring and reporting for adverse events in the study patients.
  - Pharmacists: receive, account for, prepare, and distribute study product; train study staff on study product administration procedures.
  - Data manager: maintain study databases with quality control and quality assurance procedures; prepare regular reports of ongoing study activities and data.
  - Data officers/assistants: scan data collected on paper forms for entry into electronic database(s), maintain copies of study documents as needed, prepare study documents and ensure all in correct format for study participant files, perform quality control checks in the study participants’ CRF`s.
  - Study nurses: perform screening, enrollment, follow-up and interim study visit procedures, conduct informed consent process, conduct all home visits and study retention efforts.
  - HTC counselors: perform HIV test pre-counseling, testing and post-test counseling per study protocol and Malawi national guidelines.
  - Fieldworkers: perform home follow up visits.

In addition to the full-time staff, the project will use the expertise of additional Save the Children (SC) personnel to assist with meeting study goals. A portion of SC staff’s time will be for operational and grant management services, which will provide a range of support activities to the project such as accounting, human resources management, information technology, administration and audit services.

Government staff at the study site hospital will also be engaged with this study. KCH service providers will be responsible for recruiting of study participants at KCH or BDH and managing participants’ care while in the hospital.

- **Training**

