The same treatment failure definition as above will be used for these subgroups analysis. Subgroup classification will be obtained from the screening data.

Additional subgroups not defined in either the approved protocol or statistical analysis plan will be considered post-hoc. Statisticians will keep a list of post-hoc analysis requested by investigators during the study duration.

1. **ENDPOINTS AND COVARIATES**

*6.1 Primary endpoint*

The primary endpoint will be the proportion of children failing treatment, defined as the development of any of the following before or on day 6:

- - - - WHO Integrated Management of Childhood Illness (IMCI) danger signs
      - Severe respiratory distress (e.g., grunting, nasal flaring, head nodding, or severe chest-indrawing).
      - Oxygen saturation < 90% by pulse oximetry
      - Vomiting within 30 minutes of 3 or more scheduled (i.e., not repeat) dose administrations of study product
      - Change in antibiotics prescribed by a study clinician (e.g., switch to a second-line antibiotic or prescription for onset of a co-infection)
      - Death

At or after initial hospitalization discharge assessment (between 42 and 60 hours post-enrollment):

- - - - Documented axillary temperature > 38 ºC with chest-indrawing

At day 6 outcome assessment:

- - - - Documented axillary temperature > 38 ºC
      - Chest-indrawing

The primary endpoint will be calculated from day 2, 4, 6 follow-up forms. The presence of any of the above criteria at any point prior to day 6 will constitute treatment failure. In addition to the overall treatment failure rate by day 6, we will also examine the treatment failure rates at 2 and 4 for both treatment arms.

Covariates for primary analysis: In addition to the treatment variable, the primary analysis will include (be adjusted for) the following covariates: age (2 months up to 12 months, 12 months up to 3 years, 3 years up to 5 years) and site (Bwaila District Hospital and Kamuzu Central Hospital). Of note, these are the same variables that are used for stratifying randomization. In addition, we will adjust for gender, as gender has been shown to be related to pneumonia mortality[1].

*6.2 Secondary endpoints*

The trial has the following several secondary endpoints

1. Proportion of children with clinical relapse between treatment failure assessment and day 14 follow-up visit among all children without treatment failure before or on day 6.

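### Antibiotics started by anyone other than a study clinician do not count as failure, and uncounted rescue after the Day 3 discharge could mask excess failures in the 3-day arm

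*Combined protocol and SAP*

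**What the plan says.** All three statements of the primary endpoint carry the same restriction. Protocol section 3 (Study Endpoints) lists "Change in antibiotics prescribed by a study clinician (e.g., switch to a second-line antibiotic or prescription for onset of a co-infection" among the criteria that apply at any time up to Day 6. Protocol 5.1 (Objectives and Endpoints) has "change in antibiotics prescribed by a study clinician, or death". SAP 6.1 again has "Change in antibiotics prescribed by a study clinician". Protocol 5.1 adds that "children who do not fail on assessment at day 6 will be considered clinically cured".

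The protocol also foresees care by others:

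- Section 4.6 (Management of Study Participants During Hospitalization) has study clinicians told about "any clinical decisions made by hospital staff".
- Section 6 (Protection against Risks) says "Study staff will be informed about any decisions regarding treatment failure and changing antibiotic regimens made by KCH staff".
- Appendix III says "KCH service providers will be responsible for recruiting of study participants at KCH or BDH and managing participants’ care while in the hospital".
- Section 4.10 (Adverse Events) encourages caregivers, where feasible, to bring the child to where the study clinician is based, which accepts that some care will happen elsewhere.

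Readmission is reportable as an SAE (4.10) but is not a failure criterion in section 3 or SAP 6.1. The sensitivity analyses named in SAP section 9 concern imputation assumptions and complete cases. Table 2 of SAP Appendix A lists, as reasons for failure, a change of antibiotics with no limit on prescriber, and prolonged hospitalization or readmission for pneumonia. Neither matches SAP 6.1.

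**The concern.** No passage says how an antibiotic started by a non-study prescriber is scored. By default the child counts as a success unless another criterion is documented. Take a child who worsens on Day 4, receives an antibiotic at another facility, and shows no fever, indrawing or danger sign when next examined. The treatment that rescued the child also removes the evidence of failure.

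Timing is what makes this matter. Both arms take active drug on Days 1 to 3 (Table 1 of the protocol), and discharge is assessed on the morning of Day 3. Harm from the shorter course can appear only from Day 4, when study staff see most children only at the Day 4 and Day 6 visits. If the 3-day arm is truly worse, losing the same share of late failures in each arm removes more events from that arm. At stake is the one-sided 2.5% error rate for a non-inferiority claim.

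**Working it through.** **Inputs from the plan.** 950 evaluable children per arm, 8% control failure and a relative margin of 1.5 (protocol 4.5); one-sided alpha 0.025 (protocol 5.1, SAP 7.2).

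**Inputs assumed.** The split of failures into early (both arms on active drug) and late, and the share f of failures rescued elsewhere and not counted. The documents give neither.

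**Formula.** With counted rates c (5-day) and t (3-day):

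- SE = sqrt{[c(1−c) + t(1−t)]/950}
- P(non-inferiority) = Φ[(0.5c − (t − c))/SE − 1.96]

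The margin 0.5c is treated as fixed.

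**Reproducing the plan's power.** At 8% in both arms, SE = sqrt(2 × 0.08 × 0.92/950) = 0.01245. Then 0.04/0.01245 = 3.213, and Φ(3.213 − 1.96) = 89.5%. The protocol states 88%. A simulation of the three looks with the bounds in SAP 7.2 gives 87.4%. At a 4% failure rate the formula gives 60.4% against a stated 64.8%; that figure was not reproduced and is not used here.

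**Truth at the margin.** At 8% against 12% the false-claim rate is 2.5%. For late rescue, 4 points per arm occur early and are counted, so c = 0.04 + (1−f) × 0.04 and t = 0.04 + (1−f) × 0.08. At f = 0.2, c = 0.072 and t = 0.104. SE = sqrt[(0.072 × 0.928 + 0.104 × 0.896)/950] = 0.01298. The result is Φ[(0.036 − 0.032)/0.01298 − 1.96] = Φ(−1.652) = 4.9%.

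| What is not counted | 5-day | 3-day | Ratio | False claim |
| --- | --- | --- | --- | --- |
| Nothing | 8.0% | 12.0% | 1.50 | 2.5% |
| 10% of late failures | 7.6% | 11.2% | 1.47 | 3.5% |
| 20% of late failures | 7.2% | 10.4% | 1.44 | 4.9% |
| 30% of late failures | 6.8% | 9.6% | 1.41 | 6.9% |
| 40% of late failures | 6.4% | 8.8% | 1.38 | 9.7% |
| 20% of early failures only | 7.2% | 11.2% | 1.56 | 1.2% |
| 20% of all failures | 6.4% | 9.6% | 1.50 | 2.5% |

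In the last row the error is unchanged, but power at equal true rates of 8% falls from 89.5% to 81.3%.

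**Sensitivity to the assumptions.** With 5 early points per arm, missing 10%, 25% or 50% of late failures gives 3.8%, 7.0% or 17.8%. With 3 to 6 early points and the same shares, the range is 3.2% to 22.5%. If the test allows for sampling error in the margin, the f = 0.2 case uses sqrt[(2.25 × 0.072 × 0.928 + 0.104 × 0.896)/950] = 0.01601. That gives Φ(0.004/0.01601 − 1.96) = 4.4% instead of 4.9%, so the pattern is the same.

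**Counting every outside antibiotic in the primary endpoint.** Suppose this adds 1 failure point unrelated to treatment duration to each arm. Rates become 9% and 13%, the ratio is 1.44 and the false-claim rate is 5.4%. With 2 points (10% and 14%) it is 9.9%.

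**The case against.** A reader might infer that the restriction favours non-inferiority whenever a rescue goes uncounted, including changes made by hospital staff. The documents do not support that. During the initial stay both arms take the same active drug, so missing failures then raises the ratio and works against the 3-day arm. Section 4.6 also puts study clinicians primarily in charge during any hospitalization, and section 6 gives study staff primary responsibility for inpatient management. Appendix III is in tension with this, and the passages need reconciling, but it does not establish routine prescribing by non-study staff.

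The gap at home is also narrower than the wording alone suggests. Danger signs, severe respiratory distress, saturation below 90% and death count at any time to Day 6, and fever with indrawing counts from the discharge assessment on. History and examination take place on Days 4 and 6. There is a 24-hour phone line, and interim visits are available on request and reimbursed. A missed child must worsen, be treated elsewhere, and show no criterion when examined.

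Finally, limiting the criterion to trained, blinded clinicians is a defensible choice for specificity. The last calculation shows that counting every outside antibiotic can itself move the result toward non-inferiority.

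All of this stands. It limits the direction and likely size of the problem, but it does not fill the gap in scoring. The other criteria depend on signs still being present when the child is seen, and no planned analysis tests the effect. The protocol announces sub-studies validating eligibility and outcome in 10% of children and refers to the SAP for the analyses, but the SAP describes none.

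**Conclusion.** The concern holds for rescue by other providers after the Day 3 discharge. Under the plan as written, such a child is scored as cured if no other criterion is documented by Day 6, and this can mask a true excess in the 3-day arm. With 4 early points per arm and 10% to 40% of late failures missed, the false-claim rate is about 3.5% to 9.7% against a nominal 2.5%. These are scenarios: the size cannot be derived from the documents, which give neither a rate of outside prescribing nor the timing of failures.

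Two stronger conclusions do not follow. The excess is reduced, not removed: at 20% missed it falls from 4.0 to 3.2 points. Nor does the finding show that the primary definition must be widened, since that has a comparable bias of its own. The plan needs the data and a prespecified analysis that would show whether the restriction affects the result.

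**What to change.** 1. **Record.** At the Day 2, 4 and 6 visits, within the medical history already taken, record any non-study systemic antibiotic started on or before Day 6: drug, date, indication, and prescriber or source.
2. **Report.** Tabulate these by arm and by type of prescriber.
3. **Analyse.** Add to SAP section 9, before unblinding, a sensitivity analysis of the primary endpoint that counts any such antibiotic as failure. Add a second version limited to antibiotics given for respiratory illness or worsening, which is less exposed to dilution by unrelated prescriptions.
4. **Reconcile.** Make SAP 6.1 and Table 2 of SAP Appendix A agree on antibiotic changes and on readmission or prolonged stay for pneumonia. Reconcile Appendix III with sections 4.6 and 6 on who manages inpatients.
5. **Leave** the primary definition otherwise unchanged.

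The cost is one CRF item, one extra analysis in two versions, and the wording changes.
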